### PK Analysis

AUC0-4, Tmax, Cmax and Cmin will be calculated for each subject using non-compartmental methods.

### Adverse Events

All adverse events (AEs) observed by the Principle Investigator or reported by the patient will be documented with respect to onset, severity, relationship to study treatment and resolution. Grading of severity will be performed according to the Common Toxicity Criteria (CTC) version 2.0 April 1999 (Appendix 2)

# STUDY MEDICATION

## Dosage and Formulation

### Dosage

Four treatment regimens will be evaluated in this study.

- Vehicle
- prGCD 15 units/kg body weight
- prGCD 30 units/kg body weight
- prGCD 60 units/kg body weight

A unit is defined as the amount of enzyme that catalyzes the hydrolysis of 1 micromole of the synthetic substrate para-nitrophenyl-beta-D-glucopyranoside (pNP-Glc) per minute at 37oC. Human prGCD vials are stored lyophilized at 4oC. The human prGCD final concentration is 40 unit/ml after reconstitution with WFI (or 0.9% NaCl). The final concentration and administration volumes are supplied in 200unit/vial.

### Formulation

Human prGCD is a purified recombinant, plant cells-expressed glucocerebrosidase, which is described in detail in the Investigator Brochure.

Each vial contains the following lyophilized contents:

200U of human prGCD

195 mg mannitol

35 mg sodium citrate

0.53 mg polysorbate 80, NF

The accuracy of preparation of the supplied formulations is the responsibility of the Sponsor.

## Study Drug Administration

Human prGCD will be administered as an intravenous infusion (IV) delivered over 1.5 hours. The rate of infusion is to be 135 mL/1.5 hrs (1.5ml/minute). The infusion rate will be the same over 90 minutes for all doses. The infusion rate may be adjusted according to subject symptoms and signs: slower rate (1mL/min) upon adverse effect or faster (2mL/min.) upon lack of any symptom and signs. Subjects will be monitored for 24 hours from the commencement of the infusion of each dose at the Hadassah medical center, Phase I unit.

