# STUDY DESIGN

The proposed investigation will be a phase I, single-center, non-randomized, open label, safety study of three single escalating doses of human prGCD administered as an intravenous infusion (IV) to six healthy volunteers. Subjects meeting the entry criteria will be eligible to receive study drug. Urine will be collected 24 hours prior to screening to assess renal function. Seven visits are scheduled for this study: pre-screening (Day -1), Screening (Day 0), baseline (Day 1), Visit 1 (Day 8), Visit 2 (Day 15), Visit 3 (Day 22) and follow-up visit (Day 29). The study procedures for each visit are presented in the study flow chart (Appendix 1). The duration of study is 29 days.

Subjects will be monitored over 24 hours from the commencement of the infusion of each dose at the Hadassah medical center, Phase I unit. The treatment will consist of a single dose infused for 1.5 hours (1.5mL/min). The infusion rate may be adjusted according to subject symptoms and signs: slower rate (1mL/min) upon adverse effect or faster (2mL/min.) upon lack of any symptom and signs. The vital signs for each subject will be monitored during infusion. ECG will be done at baseline and at 8 hours following the infusion. Subjects will remain at the clinic for 8 hours post-infusion and will be discharged if no AEs are observed. Subjects will return to the clinic 24h post initiation of infusion for additional safety assessment. Vital signs will be recorded during the infusion and PK sampling every 30 minutes (up to 3.5 hrs), and afterward at 8 and 24hrs post infusion.

Each subject will receive a single IV dose of vehicle at the baseline visit (Day 1). Blood samples for PK will be collected prior to dosing (0) and at 5, 45, 80 and 90 minutes during the infusion and 100, 115, 130, 150, 180, 210 minutes and 24 hours from initiation of infusion. On Day 8, subjects will receive a single 15 units/kg of study drug and will have the same blood samples taken as per Day 1. On Day 15, subjects will receive a single 30 units/kg of study drug and have the blood samples taken as per Day 1. On Day 22, subjects will be administered a single dose of study drug of 60 units/kg, and have the same procedures performed as Day 1.

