The Principle Investigator will review all test results and AE report 24h prior to escalation to the next dose level. The dose will be increased based on review of drug toxicity by the Principle Investigator and the Medical Director of Protalix Ltd. A follow up safety visit will take place at Day 29.

Plasma levels of human prGCD will provide a pharmacokinetic profile, including AUC0-inf, Tmax, Cmax and Cmin and will be calculated for each subject.

All PK samples of human prGCD will be analyzed at the end of the study for all subjects. This data will be used as adjunct information for a safety review, which will include a review of adverse events, changes in vital signs, physical examination and clinical laboratory test results. Unexpectedly high plasma concentrations will be reviewed for correlation to related adverse events.

This study is conducted according to FDA and European GCP guidelines.

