## Preparation and Labeling

Reconstitution with 5.1mL of Sterile Water for Injection (WFI) yields a final volume of 5.1 mL human prGCD (40 units/mL), which provides a withdrawal volume of 5.0 mL (200 enzyme units). The solution must be mixed well until clear. The required amount of enzyme units will be adjusted with normal saline (0.9%) up to 135ml/infusion.

In case a subject will weigh over 90 kg at dosing of 60 units/kg infusion volume will be increased to 150mL accordingly.

Vehicle preparation includes reconstitution as described herein above for the human prGCD, where the number of vials containing vehicle formulation is equivalent to the number of vials that are required for administering 60U/kg for each subject.

prGCD

Enzyme 6mg, 200 units

195mg Mannitol

35mg Sodium Citrate

0.53mg Polysorbate 80 N.F.

Batch # PLX-GC-XXX-XXXX Date_____

Protocol # P-01-2005

For Clinical use only

Storage 2-8oC

[figure not shown]

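### Infusion rate, length and volume do not agree, so fixed-clock PK samples change phase, and Cmax and Tmax mix dose with infusion rate, whenever the rate is altered or 150 mL is used

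*Protocol*

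**What the plan says.** **Default.** The synopsis (Dose) and section 6.2 give 135 mL over 1.5 hours, that is 1.5 mL/min. Section 6.2 adds: "The infusion rate will be the same over 90 minutes for all doses".

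**Exception.** The next sentence of section 6.2 permits a "slower rate (1mL/min) upon adverse effect or faster (2mL/min.) upon lack of any symptom and signs". Section 3 repeats it: "The infusion rate may be adjusted according to subject symptoms and signs". The synopsis does not mention it.

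**Larger volume.** Section 6.5: "In case a subject will weigh over 90 kg at dosing of 60 units/kg infusion volume will be increased to 150mL accordingly". No rate or duration is given for the 150 mL. Sections 4.1 and 4.2 set no weight limit.

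**PK sampling.** Draws are at 0, 5, 45, 80 and 90 minutes, labelled as during the infusion, then at 100, 115, 130, 150, 180 and 210 minutes and 24 hours. Section 3 and footnote f of Appendix 1 count the later draws from the start of infusion. The synopsis (Design) and section 5.4 call them post-infusion.

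**Use of the data.** Cmax, Tmax and AUC are planned per subject (sections 3, 5.6.2, 9.3 and 9.4.3). Section 3 adds: "Unexpectedly high plasma concentrations will be reviewed for correlation to related adverse events".

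**The concern.** A single rate over 90 minutes for every dose cannot hold alongside 1 or 2 mL/min, nor alongside 150 mL at 1.5 mL/min. The sampling clock does not move with the infusion. If an infusion is sped up, the 80- and 90-minute draws come after it has ended and the peak may fall in the gap between 45 and 80 minutes. If it is slowed, draws meant to follow the infusion are taken during it.

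Each subject receives all three active doses, so a rate that differs between visits is confounded with dose in Cmax and Tmax. The rate also depends on symptoms: an adverse effect lowers later concentrations, and absence of symptoms can raise them. That dependence could weaken the relation the section 3 review looks for.

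The faster option is triggered by absence of symptoms, which is a likely state in healthy volunteers. A rate change is therefore not a remote possibility.

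**Working it through.** **1. The plan's own figure.** Length = volume / rate = 135 / 1.5 = 90 min. The default case agrees with itself.

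**2. Permitted rates, held throughout (135 mL).** 135 / 1 = 135 min; 135 / 2 = 67.5 min.

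**3. Rate changed during the infusion.** For a change at *s* minutes to rate *r*, end = *s* + (135 − 1.5*s*) / *r*.
- *s* = 30 leaves 90 mL: the end is at 30 + 90 = 120 min (slow) or 30 + 45 = 75 min (fast).
- *s* = 45 leaves 67.5 mL: the end is at 45 + 67.5 = 112.5 min (slow) or 45 + 33.75 = 78.75 min (fast).

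**4. The 150 mL volume.** 150 / 1.5 = 100 min. To fit 90 min, 150 / 90 = 1.67 mL/min, which is not a stated rate.

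**5. What the volume can hold.** Section 6.1.1 gives 40 units/mL after reconstitution. 60 units/kg then needs 60*W* / 40 = 1.5*W* mL: 135 mL at 90 kg, 150 mL at 100 kg, 165 mL at 110 kg. So 150 mL holds the stated dose only up to 100 kg.

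**6. Where the draws fall.**

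| Infusion | Ends (min) | Draws out of their labelled phase |
| --- | --- | --- |
| 135 mL, 1.5 mL/min | 90 | none |
| 135 mL, 1 mL/min throughout | 135 | 100, 115, 130 are during infusion |
| 135 mL, slowed at 30 min | 120 | 100, 115 are during infusion |
| 135 mL, slowed at 45 min | 112.5 | 100 is during infusion |
| 135 mL, 2 mL/min throughout | 67.5 | 80, 90 are after the end |
| 135 mL, sped up at 30 or 45 min | 75 or 78.75 | 80, 90 are after the end |
| 150 mL, 1.5 mL/min | 100 | 100 is at end of infusion |

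**7. Size of the effect.** The protocol gives no half-life, so 5 to 60 min is an assumption. The model is one-compartment and linear, with *k* = ln 2 / t½. Within a segment at rate *r*, C rises as (*r* / *k*)(1 − e^(−*kt*)) plus the decayed carry-over from the previous segment; after the end it decays as e^(−*kt*). The total dose is the same in every case. Sampled Cmax is the largest value on the protocol's clock up to 210 min, divided by the same quantity for the 90-min infusion.

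| t½ (min) | Slowed at 30 | Slowed at 45 | Sped up at 30 | Sped up at 45 |
| --- | --- | --- | --- | --- |
| 5 | 0.71 | 1.00 | 1.29 | 1.12 |
| 10 | 0.74 | 0.96 | 1.17 | 1.19 |
| 20 | 0.70 | 0.83 | 1.05 | 1.17 |
| 40 | 0.77 | 0.78 | 1.05 | 1.11 |
| 60 | 0.81 | 0.82 | 1.04 | 1.07 |

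Sampled Tmax is 90 min for the default. It lies between 45 and 115 min when slowed and at 45 or 80 min when sped up. AUC to 210 min (linear trapezoid) is 0.95 to 1.02 of the default when slowed and 0.91 to 1.01 when sped up.

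**8. Vial content.** Section 6.1.2 lists "200U of human prGCD" per vial. Section 6.5 reconstitutes it to 5.1 mL and states 40 units/mL and 200 units in a 5.0 mL withdrawal. But 200 / 5.1 = 39.2 units/mL, and 39.2 × 5.0 = 196 units. The statements agree only if the vial holds 40 × 5.1 = 204 units.

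**The case against.** The best defence is that this is a default with a tolerability exception. The sentence about one rate for all doses can be read as the rule across dose levels, and the next sentence as permission to depart from it. That reading removes much of the verbal contradiction. It does not supply a length for the 150 mL, and it does not move the sampling clock when the rate moves.

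A second defence is that section 7.3 records the time of onset of an adverse event and any action taken with the study drug, and that use of actual times may sit in a CRF, PK manual or SAP that is not shown. This stands in part. It would capture a slowing caused by an adverse event, but not a speeding-up without one. Nor can a later analysis document recover a peak that fell between scheduled draws.

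A reader might infer three stronger things that the documents do not support:

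- **That the concentration-AE review is biased or reversed.** The effect arises only if rates are changed. The review is adjunct and descriptive in six subjects, and section 9.4.4 calls all analyses exploratory. No reversal is demonstrated.
- **That Cmax would run from 0.67 to 1.33 of nominal.** Those extremes come from holding 1 or 2 mL/min from time zero. Slowing follows an adverse effect, so some time at 1.5 mL/min normally comes first. Plans of this kind also use sampled, not true, Cmax: with 2 mL/min from time zero and an assumed 40-minute half-life, sampled Cmax is 0.94 of nominal, so the rise disappears.
- **That delivered doses will be wrong.** At 110 kg, 150 mL would hold 150 × 40 / 110 = 54.5 units/kg, but section 6.5 prepares the required units, so the volume might give way instead. This needs a subject above 100 kg among six. The 2% vial discrepancy disappears if vials hold 204 units.

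**Conclusion.** The concern holds in a conditional form. By the protocol's own arithmetic, rate, length and volume do not fit together once the rate is altered or 150 mL is used, and the reference time for the later PK draws is stated in two ways. If either condition occurs, some samples fall in a phase other than the one labelled, and Cmax and Tmax mix dose with infusion rate.

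For a change at 30 to 45 minutes, sampled Cmax is about 0.70 to 1.00 of nominal when slowed and 1.04 to 1.29 when sped up, with a smaller effect on AUC. These figures rest on an assumed one-compartment model and assumed half-lives of 5 to 60 minutes; they illustrate the size and do not predict it. Because the rate follows symptoms, the descriptive concentration-AE review could be weakened; more than that is not shown. The vial arithmetic is a minor point. The matter should be corrected, but it does not undermine the trial.

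**What to change.** The sponsor should reconcile:
- the synopsis (Dose) and sections 3, 6.2 and 6.5 on infusion rate, length and volume, including subjects above 90 kg and above 100 kg; no view is taken here on which rate, volume or rule is right;
- the synopsis (Design), sections 3 and 5.4 and Appendix 1 footnote f on whether later PK draws count from the start or the end of infusion;
- sections 6.1.2 and 6.5 on vial content.

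Whatever is chosen:
- record the actual start, stop and every rate change, with actual sampling times;
- time the end-of-infusion and later PK draws from the actual stop;
- use actual times and delivered units in the non-compartmental analysis;
- flag rate-altered infusions in the Cmax and Tmax summaries and in the concentration-AE review. Recording times corrects the phase error but not the dependence of rate on symptoms, so the flag is needed as well.

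The cost is protocol and preparation wording, a few CRF fields and a small amount of extra analysis.

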## Blinding

Not applicable

## Packaging

Lyophilized drug powder is stored in 20 ml low extractable borosilicate glass bottles (Wheaton Science Product, USA or Bunder Glass, Germany). Lyophilization stoppers (Wheaton Science Product, USA) composed of two-leg grey butyl rubber are sealed with Tear-Cap Aluminum seals (Wheaton Science Product, USA).

## Preparation and Labeling

Reconstitution with 5.1mL of Sterile Water for Injection (WFI) yields a final volume of 5.1 mL human prGCD (40 units/mL), which provides a withdrawal volume of 5.0 mL (200 enzyme units). The solution must be mixed well until clear. The required amount of enzyme units will be adjusted with normal saline (0.9%) up to 135ml/infusion.

In case a subject will weigh over 90 kg at dosing of 60 units/kg infusion volume will be increased to 150mL accordingly.

Vehicle preparation includes reconstitution as described herein above for the human prGCD, where the number of vials containing vehicle formulation is equivalent to the number of vials that are required for administering 60U/kg for each subject.

prGCD

Enzyme 6mg, 200 units

195mg Mannitol

35mg Sodium Citrate

0.53mg Polysorbate 80 N.F.

Batch # PLX-GC-XXX-XXXX Date_____

Protocol # P-01-2005

For Clinical use only

Storage 2-8oC

[figure not shown]

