# SUBJECT POPULATION

## Inclusion Criteria

The following are the inclusion criteria:

1. Healthy male or female between 18 and 45 years of age.
2. Female subjects must agree to use a medically acceptable method of contraception at all times during the study and must have a negative serum pregnancy test at baseline and during the study period.
3. Females of child-bearing potential must be non-pregnant and not lactating and using adequate birth control such as oral contraceptives
4. Negative laboratory tests for HIV, HBsAg or HCV
5. Naïve to any previous recombinant protein therapy
6. Provide written informed consent
7. Have the ability to understand the requirements of the study and to comply with the study protocol and dosing regimen

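### Section 6.5 fixes 150 mL for every subject over 90 kg at 60 units/kg, but that volume holds the full dose only up to 100 kg, and no weight limit is set

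*Protocol*

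**What the plan says.** Section 6.1.1 (Dosage) gives the strength: "The human prGCD final concentration is 40 unit/ml after reconstitution". Section 6.5 (Preparation and Labeling) agrees, describing a reconstituted vial "which provides a withdrawal volume of 5.0 mL (200 enzyme units" in all). The same section sets the standard volume: "The required amount of enzyme units will be adjusted with normal saline (0.9%) up to 135ml/infusion". It then makes one exception: "In case a subject will weigh over 90 kg at dosing of 60 units/kg infusion volume will be increased to 150mL accordingly".

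Section 6.2 (Study Drug Administration) sets the timing for the standard volume: "The rate of infusion is to be 135 mL/1.5 hrs (1.5ml/minute"), and adds "The infusion rate will be the same over 90 minutes for all doses". It allows adjustment by symptoms and signs: "slower rate (1mL/min) upon adverse effect or faster (2mL/min.) upon lack of any symptom and signs".

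Section 4.1 opens with "Healthy male or female between 18 and 45 years of age". Neither Section 4.1 nor Section 4.2 names a weight or BMI limit. The last exclusion leaves general suitability to the investigator without mentioning weight.

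**The concern.** The exception in Section 6.5 exists because a heavy subject's dose at 60 units/kg no longer fits in 135 mL. It has a lower bound (90 kg) and one fixed volume (150 mL), but no upper bound. A fixed volume at a fixed strength carries a fixed maximum number of units, so a dose defined per kg must outgrow it at some weight. If that weight is one the eligibility criteria admit, the site has two instructions that it cannot both follow.

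What is at stake is the preparation of the highest escalation step in the first trial of this plant-cell-derived enzyme. The site would have to exceed the written volume or give less than 60 units/kg. A smaller, related gap is that Section 6.2 gives its rate and duration for 135 mL and does not say how a 150 mL infusion should be run.

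**Working it through.** **Inputs, all from the protocol**
- Units withdrawn per vial: 200 in 5.0 mL (Section 6.5)
- Top dose: 60 units/kg (Section 6.1.1)
- Volumes: 135 mL standard; 150 mL over 90 kg at 60 units/kg (Section 6.5)
- Rate: 1.5 mL/min for 135 mL, adjustable to 1 or 2 mL/min (Section 6.2)
- Weight limit: none (Sections 4.1 and 4.2)

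**Step 1: volume of drug per kg.** 200 / 5.0 = 40 units/mL, and 60 / 40 = 1.5 mL/kg.

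**Step 2: reproduce the protocol's threshold.** Maximum weight for a volume V is V × 40 / 60. For 135 mL: 135 × 40 / 60 = 90 kg (5400 units, 27 vials). This matches the stated 90 kg exactly, so the rule rests on undiluted drug at 40 units/mL.

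**Step 3: apply the same formula to 150 mL.** 150 × 40 / 60 = 100 kg (6000 units, 30 vials).

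**Step 4: above 100 kg.** Weights are illustrative, because the protocol gives no expected weights.

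| Weight | Volume needed (1.5 × kg) | Dose if 150 mL is kept (6000 / kg) | Shortfall |
| --- | --- | --- | --- |
| 100 kg | 150 mL | 60.0 units/kg | none |
| 101 kg | 151.5 mL | 59.4 units/kg | 1% |
| 110 kg | 165 mL | 54.5 units/kg | 9% |
| 120 kg | 180 mL | 50.0 units/kg | 17% |

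**Step 5: lower doses.** At 30 units/kg, 135 mL holds the dose up to 135 × 40 / 30 = 180 kg, so the problem is confined to the 60 units/kg step.

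**Step 6: sensitivity to strength.** If 200 units were spread over the full 5.1 mL, the strength would be 200 / 5.1 = 39.2 units/mL. The limits would then be 88.2 kg for 135 mL and 98.0 kg for 150 mL. The conclusion is unchanged, and the protocol states 40 units/mL.

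**Step 7: timing at 150 mL.** At a constant 1.5 mL/min, 150 / 1.5 = 100 minutes. In 90 minutes, the average rate must be 150 / 90 = 1.67 mL/min. With the permitted increase, 60 min × 1.5 + 30 min × 2 = 90 + 60 = 150 mL in 90 minutes. For comparison, Section 6.2 already lets a 135 mL infusion run from 135 / 2 = 67.5 minutes to 135 / 1 = 135 minutes.

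**The case against.** The strongest reply is that the regimen is defined in units/kg and the volume is a preparation detail. A pharmacist counting vials would probably draw 33 vials for a 110 kg subject and record a volume departure. That is likely right, and the documents do not support a claim that heavy subjects would be silently underdosed. What stands is that the protocol would force a departure in order to deliver its own dose.

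It can also be said that the closing word of the Section 6.5 sentence implies scaling with weight. But the sentence names a single volume and gives no per-kg rule. Investigator discretion could keep a very heavy volunteer out, but it is not a limit, and Section 6.5 plainly expects subjects over 90 kg.

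On timing, a reader might infer that 1.5 mL/min and 90 minutes are irreconcilable at 150 mL. That is true only at a constant rate. Section 6.2 ties its rate to 135 mL, and its 2 mL/min option lets a symptom-free subject receive 150 mL in 90 minutes (step 7). What remains is that the planned starting rate and duration for 150 mL are not stated.

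A reader might also infer that PK sampling would lose alignment with the end of infusion. The documents do not support this as a distinct harm: the existing rate adjustments already allow far more than the 10 minutes at issue.

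**Conclusion.** The point holds as a minor one. At the stated 40 units/mL, 150 mL delivers 60 units/kg up to 100 kg and no further, and eligibility does not stop at 100 kg. Above that weight, the volume and the dose in the protocol contradict each other. For subjects over 90 and up to 100 kg, the 150 mL volume is adequate.

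The reach is small. Dose is affected only if one of the six volunteers exceeds 100 kg, and planned duration only if one exceeds 90 kg. If nobody does, the effect is nil. The shortfall, should a site keep to 150 mL, is 1% at 101 kg and 9% at an assumed 110 kg. The analysis is descriptive, and no endpoint or stopping rule is shown to change. The conclusion rests on reading 150 mL as one fixed volume, which is what the text says.

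**What to change.** Choose one of two changes.
1. Add an eligibility limit so that dosing-day weight at 60 units/kg does not exceed 100 kg. Because weight can change between screening and Day 22, the screening limit should sit somewhat below 100 kg; the protocol gives no basis for the margin, so the sponsor should set it. The cost is possibly a few exclusions.
2. Keep 150 mL, made up with saline, for subjects over 90 and up to 100 kg, and state that above 100 kg the volume is 1.5 mL per kg of dosing-day weight. The cost is a longer infusion in the heaviest subjects.

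Under either choice, state that any volume over 135 mL starts at the Section 6.2 rate of 1.5 mL/min with the duration extended (100 minutes at 150 mL; 165 / 1.5 = 110 minutes at an assumed 110 kg). This remains subject to the existing symptom-based adjustment and never goes above 2 mL/min. Holding 90 minutes instead is not advised. It would plan 1.67 mL/min at 150 mL before absence of symptoms is shown, would reach 180 / 90 = 2.0 mL/min at 120 kg, and would pass the fastest permitted rate beyond that.

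As a clarification only, say that the same volume and timing apply to that subject's vehicle infusion. The vehicle vial count already follows 60 units/kg (95 kg: 95 × 60 / 200 = 28.5 vials, × 5.0 = 142.5 mL), while the 150 mL sentence mentions only the 60 units/kg dose.

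The whole change is a few sentences in Section 6.5, plus one criterion in Section 4 if the limit is chosen. No new measurement is needed, because body weight is already taken at screening and at each treatment visit.
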